## Specific objective

1. To develop web-based education videos for type 2 diabetes patients in primary care.
2. To identify the sociodemographic characteristics (age, gender, ethnicity, education level, marital status, employment status, income, smoking status, history of hospitalisation due to complication of type 2 diabetes) of the type 2 diabetes patient in the primary care clinic among intervention and control groups at baseline.
3. To determine the knowledge scores and clinical outcome (HbA1c, blood pressure, fasting lipid profile, BMI, waist circumference) among intervention and control groups at baseline.
4. To investigate the effectiveness of web-based education videos and compare on the knowledge, diabetes empowerment and clinical outcome (HbA1c, blood pressure, fasting lipid profile, BMI, waist circumference) at baseline, 3months and 6 months between and within the intervention and control groups.

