## Inclusion Criteria

Those eligible for enrolling are type 2 diabetes patients aged 18 years or older, who have been diagnosed and followed up for type 2 diabetes for at least six months, have an HbA1c greater than 8% at the time of enrolment, and only one family member from each household will participate in the study. Furthermore, they should be able to understand Malay and have internet access at home.

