## Sample Size

Sample size was calculated based on two mean groups formula (20) , mean±sd of knowledge differences for intervention group and control group were 0.7±2.21 and -0.30±2.33 (16), 80% of power, 5% of risk error, 30% attrition rate, the sample size needed per group is 116 (total is 232).

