## Data collection method

Data will be collected by the research by selecting type 2 diabetes patients from the baseline. These type 2 diabetes patients will have to meet the inclusion and exclusion criteria, once it is fulfilled the type 2 diabetes patients will be recruited. A research assistant will approach patients on the day of their follow-up visit at Klinik Kesihatan Cheras Baru. As part of the consent process, the investigator will explain and provide the Patient Information Sheet to the participant and an agreement to receive calls and messages from the researcher for research purposes. They will keep their phone numbers private and will only be contacted or messaged every four weeks to remind them to complete the videos watching and follow-up appointment. The patients will, however, be given one week to consider their participation if they are still deciding on the recruitment day. We will conduct a one-to-one ratio randomization control trial with the control and intervention groups.

During the same day, all participants will be given a hard copy self-administered questionnaire by research assistance to complete and their latest clinical profile (height, weight, BMI, waist circumference, blood pressure, latest blood test for HbA1c and fasting lipid profiles) will be taken from their medical records. The self-administered questionnaire will take about 20minutes to complete. This stage will be considered as baseline assessment for both control and intervention groups. After the questionnaire, both groups will continue their follow up in the clinic like usual. The intervention group will take place after all the participants complete the questionnaire. The participants will be told about the structure of the program. There will be a research assistant who the researcher has already trained to assist and teach the participants how to assess and use the web-based online education videos. They will need to watch all the videos. The research assistant will follow up with their progress and remind them to complete the video in every four weeks via phone call.

After three months of the intervention on the first week of September (2/9/2024 to 6/9/2024), both of the intervention and control group participants will return to the clinics for follow up. During the follow-up, participants will be given a self-administered questionnaire to answer.

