At six months’ time point from the baseline on the last week of December (23/12/2024 to 31/12/2024), both of the intervention and control group participants will return to the clinics for follow up. During the follow-up, participants will be given a self-administered questionnaire to answer and their latest clinical profile (height, weight, BMI, waist circumference, blood pressure, latest blood test for HbA1c and fasting lipid profiles) will be taken from their medical records. This is a basic diabetes education video for self-care and education, and no further treatment will be given after the study has been completed. You will continue your diabetes follow up as usual.

*Figure 2: Flow of the process*

[figure not shown]

Collection of questionnaires port write up and dissemination of result

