#### Independent Variables

Independent variable will be the web-based education video for the intervention group and a talk about diabetes educations for the control group

Intention to treat (ITT) method will be used for statistical analysis. Statistical analysis will be done using IBM SPSS Statistics version 27. Descriptive analysis will be conducted to check the error and distribution of data. Histogram with normal curve will be used for normality checking. Independent-t test will be used to investigate the difference of diabetes knowledge test between group. Paired t test will be used pretest and post-test after 6 months. Generalized Estimating Equation (GEE) will be used to investigate the effectiveness of diabetes knowledge and clinical outcome, adjusted with covariates. P<0.05 will be considered statistically significant.

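### The GEE planned for the two-visit clinical outcomes most naturally tests a difference in mean change, which is less precise than adjusting the six-month value for baseline

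*Protocol*

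**What the plan says.** Section 3.12, under Independent Variables, states: "Generalized Estimating Equation (GEE) will be used to investigate the effectiveness of diabetes knowledge and clinical outcome, adjusted with covariates". The covariates are not named, and nothing says whether baseline is a response or a covariate. The same paragraph mentions an independent t-test for knowledge and a paired t-test from pretest to six months. The paired test is not clearly limited to knowledge, but it compares time points and not arms. GEE is thus the only between-arm method named for HbA1c, blood pressure, lipids, BMI and waist circumference.

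Section 3.9 takes the "latest clinical profile (height, weight, BMI, waist circumference, blood pressure", HbA1c and lipids from the records on the first day, and adds: "This stage will be considered as baseline assessment for both control and intervention groups". For the three-month visit it provides only the questionnaire: "During the follow-up, participants will be given a self-administered questionnaire to answer". At six months, "participants will be given a self-administered questionnaire to answer and their latest clinical profile" is again taken from the records. The schedule in section 3.20 agrees, with an empty three-month cell for the clinical profile.

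Objective 4 in section 2.2 compares knowledge, empowerment and clinical outcome "at baseline, 3months and 6 months between and within the intervention and control groups". Section 3.11 lists the clinical measures only as dependent variables. Its independent variables are sociodemographic items, smoking status and hospitalisation history.

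**The concern.** With one follow-up value per person, a repeated-measures model has a second response only if baseline supplies it. Objective 4 and section 3.11 point the same way. A GEE with arm, time and arm-by-time fitted to those two values estimates the difference between arms in mean change.

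Regressing the six-month value on arm and the participant's own baseline uses the same data better. In large samples it is never less precise, and it removes the effect of a chance baseline difference between arms. The change contrast subtracts the whole of that difference, although only a fraction of it, the regression slope, is expected to persist to six months. Research question 2, on clinical outcome, rests on these variables.

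**Working it through.** **The plan's own figure.** Section 3.6 gives "mean±sd of knowledge differences for intervention group and control group were 0.7±2.21 and -0.30±2.33", with 80% power, 5% error (two-sided assumed) and 30% attrition. The pooled SD is √[(2.21² + 2.33²)/2] = 2.271 and the difference is 1.0. This gives 81 per group, and 81/0.7 = 115.7, so 116 per group is reproduced. It is sized on knowledge change and does not depend on the clinical analysis. I use 81 per arm below as the number expected to complete.

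**Inputs that the protocol does not give.** There is no SD and no baseline-to-six-month correlation for any clinical outcome. All values of ρ, slope b and SD below are assumed ranges. The mean HbA1c of 7.9% comes from section 1.1 and is a national figure, not the clinic's.

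**Precision with equal SDs at both visits.** In units of the outcome variance, change has variance 2(1−ρ) and the baseline-adjusted value has 1−ρ². The ratio of adjusted to change is (1−ρ²)/[2(1−ρ)] = (1+ρ)/2.

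| Assumed ρ | Ratio | Extra patients for the change contrast to match |
|---|---|---|
| 0.4 | 0.70 | 1/0.70 − 1 = 43% |
| 0.5 | 0.75 | 33% |
| 0.6 | 0.80 | 25% |
| 0.95 (BMI, waist) | 0.975 | about 2.6% |

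**HbA1c, given entry above 8%.** Take a normal distribution with mean 7.9 and SD 1.5 or 2.0, cut off at 8. The baseline SD among those entered is 0.89 or 1.19, so baseline variance is about 0.35 of the uncut variance. Per unit of uncut variance, the adjusted variance is 1−b² and the change variance is 1−b² + 0.35(1−b)².
- b = 0.4: 0.84/(0.84 + 0.126) = 0.87
- b = 0.5: 0.75/(0.75 + 0.0875) = 0.90
- b = 0.6: 0.64/(0.64 + 0.056) = 0.92

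A separate simulation (uncut SD 1.8, 81 per arm, 1,500 runs) gave ratios of 0.86, 0.89 and 0.94 at ρ = 0.3, 0.5 and 0.7, in line with these.

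**Effect of a chance baseline difference.** The change estimate shifts by −(1−b) per unit of baseline difference, and the adjusted estimate by about 0. In the simulation the shifts were −0.69, −0.55 and −0.32 at ρ = 0.3, 0.5 and 0.7. For HbA1c, a difference of two standard errors moves the change estimate by (1−b) × 2 × SD₀ × √(2/81), where SD₀ is the baseline SD:
- 0.4 × 2 × 0.89 × 0.157 = 0.11 percentage points
- 0.6 × 2 × 1.19 × 0.157 = 0.22 percentage points

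**What different GEEs do with two-visit data.** In 200 simulated trials (ρ = 0.6, equal variances, 81 per arm):
- Baseline as response with arm, time and arm-by-time: identical to the difference in mean change; SD of the estimate 0.140.
- Six-month value as response with baseline as covariate: identical to ANCOVA; SD 0.126.
- Baseline as response with one common baseline mean (exchangeable working correlation): SD 0.126.

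The variance ratio 0.126²/0.140² = 0.81 agrees with (1 + 0.6)/2 = 0.80.

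**The case against.** The strongest objection is that section 3.12 does not fix the weaker model. It allows unnamed covariates, baseline could be one of them, and the choice of covariates is often left to a separate SAP. A reader might infer that two visits compel a test of change. They do not, as the second and third GEEs in the working show. What remains is that sections 2.2 and 3.11 steer towards baseline as a response, and that section 3.12 is the protocol's own statistical analysis plan and names the model. The point is about that stated choice as naturally read, not about missing detail.

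A reader might also infer from the entry criterion ("have an HbA1c greater than 8% at the time of enrolment") that regression to the mean biases the HbA1c comparison. The design does not support this. Both randomised arms are selected alike, and the simulation with a true effect of −0.4 returned means of −0.39 to −0.40 under either analysis. The imbalance effect arises without any selection, and selection makes the loss of precision smaller. Nor is the imbalance a second harm on top of the wider interval: it is the source of that width, seen within one trial. A two-standard-error difference is roughly a 1-in-20 event.

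Two further points stand. The sizes rest on assumed correlations and SDs. And ANCOVA leaves out participants without a six-month value, which matters when the plan allows 30% attrition and declares intention to treat.

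**Conclusion.** The point holds as a recommendation on secondary outcomes. On its most natural reading, section 3.12 compares mean changes where adjustment for a baseline value already collected would be more precise. The loss is worthwhile to recover for blood pressure and lipids (variance ratio 0.70 to 0.80 if ρ is 0.4 to 0.6 and SDs are equal), modest for HbA1c (0.87 to 0.92 under the cut-off normal model with slope 0.4 to 0.6), and negligible for BMI and waist (2% to 3% at ρ about 0.95). The change contrast is not biased over randomisations. In a single trial it carries (1 − slope) of the chance baseline difference. The HbA1c entry criterion is not the cause, and the sample size stands.

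**What to change.** In section 3.12, state that for each clinical outcome the six-month value is compared between arms by linear regression with arm and the participant's own baseline value of that outcome as covariates (ANCOVA), reported as an adjusted mean difference with 95% CI.

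A GEE with baseline means constrained equal across arms is an alternative, and it keeps participants without a six-month value in the model, although they add almost nothing to the arm contrast. If it is chosen, the working correlation must not be independence. With an exchangeable working correlation α, the estimate is the difference in six-month means minus α times the baseline difference. At α = 0 there is no adjustment, and where the two visits' variances differ, as for HbA1c after selection, α need not equal the ANCOVA slope. ANCOVA is the simpler choice.

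Within-arm changes can still be described, as objective 4 asks. The GEE can stay for the three-visit knowledge score, with the role of baseline stated there too. The cost is a sentence or two of analysis text, with no new data, visits or patients.

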## Risk and benefit to study participants

There is minimal risk involved in this study as the chances and magnitude of harm or discomfort anticipated in the research are not greater than those ordinarily encountered in daily life of the general population or during the performance of routine physical or psychological examinations or tests. During the study, sometimes, you may be taken more time to answer the questionnaires. There may or may not be any benefits to the participants. However, the use of web-based education videos can enhance diabetes knowledge and improve clinical outcomes (HbA1c, blood pressure, fasting lipid profile, BMI, waist circumference) among patients with type 2 diabetes. There is a potential for web-based education videos to be systematically implemented in all primary care clinics to simplify patient self-management and to reduce the risk that diabetes complications.

## Ethics of Study

This study will be conducted in compliance with ethical principles outlined in the Declaration of Helsinki and Malaysian Good Clinical Practice Guideline. Ethical approval will be obtained from MREC and NMRR prior to the start of any study related activities.

## Data storage, privacy and confidentiality

Regarding data storage and use are safeguard as follows:

All investigators and study site team involved with this study must comply with the requirements of the appropriate data protection legislation with regard to the collection, storage, processing and disclosure of personal information. The participant will not be identified through personal identifiable information but will be given a study identification number. Access to collated unidentifiable participant data will be restricted to individuals from the research team treating the participants, representatives of the sponsor(s) and representatives of regulatory authorities.

All the information we have collected in paper copies will be stored under lock and key in Universiti Putra Malaysia, while the electronic data including audio recordings and transcripts will be anonymized and can only be accessed with a secure password in laptops for this research. Only the researchers and regulatory authorities and Research & Development auditors will have access to the data. Published results will not contain any personal data that could allow identification of individual participants. Data will be stored for 5 years and will be destroyed after the storage period. When publishing or presenting the study results, the participant identity will not be revealed.

## Informed Consent/Assent Process

Participants will receive patient information sheets in English or Malay, depending on their preference. They will be given ample time (1 week) to make an informed decision if they are

indecisive. Participant can contact principal investigator if any clarification needed.

## Conflict of Interest

The investigators declare they have no conflict of interest.

## Publication Policy

Permission from the Director General of Health, Malaysia will be obtained prior to publication. No personal information will be disclosed, and subjects will not be identified when the findings of the survey are published. The results will be presented from the analysis of pool data.

## Termination of Study

Participants whom who wish to withdraw from the study can withdraw from the study anytime by informing principal investigator.

## Study Outcome

## The primary outcome of interest are diabetes knowledge and diabetes empowerment.

## The secondary outcome is clinical outcome (HbA1c, blood pressure, fasting lipid profile, BMI, waist circumference) among intervention and control groups at baseline.

|  | Baseline | Three month – follow up  (2/9/2024 to 6/9/2024) | Six month – follow up  (23/12/2024 to 31/12/2024) |
| --- | --- | --- | --- |
| Questionnaire | √ | √ | √ |
| Patients’ latest clinical profile (height, weight, BMI, waist circumference, blood pressure, latest blood test for HbA1c and fasting lipid profiles) will be taken from their latest medical records | √ |  | √ |

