## Recruitment and randomisation

The study design that will be used in this study is a Blocked Randomized Control Trial (RCT) ratio one to one.

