## Statistical Analysis Plan

#### Dependent Variables

In this study, the primary outcome of interest is diabetes knowledge and the secondary outcome is clinical outcome (HbA1c, blood pressure, fasting lipid profile, BMI, waist circumference) among intervention and control groups at baseline.

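### Section 3.12 names knowledge as the only primary outcome and section 3.20 names knowledge and empowerment; the sample size and the named tests do not cover empowerment

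*Protocol*

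**What the plan says.** Section 3.20 (Study Outcome) gives two primary outcomes: "The primary outcome of interest are diabetes knowledge and diabetes empowerment". The contents list carries the same line. Section 3.12, under Dependent Variables, gives one: "the primary outcome of interest is diabetes knowledge and the secondary outcome is clinical outcome". Empowerment is not listed there as secondary either.

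The other sections bear on the two outcomes as follows.

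- **Sample size (3.6).** The planning values are for knowledge only: "mean±sd of knowledge differences for intervention group and control group were 0.7±2.21 and -0.30±2.33", with "80% of power, 5% of risk error, 30% attrition rate". The result is 116 per group, 232 in total.
- **Analysis (3.12, under Independent Variables).** "Independent-t test will be used to investigate the difference of diabetes knowledge test between group". The GEE is for knowledge and the clinical outcomes. The paired t-test is tied to 6 months but to no named outcome. The only threshold is "P<0.05 will be considered statistically significant".
- **Research questions (1.2) and operational definitions (3.11).** Neither mentions empowerment.
- **Where empowerment does appear.** Specific objective 4 (2.2) has it compared between and within groups at baseline, 3 and 6 months, without a rank. Section C of the questionnaire (3.10) describes its instrument and reliability. The schedule in 3.20 has the questionnaire completed at all three visits.

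**The concern.** The protocol gives two answers to the question of which result decides the trial. Both sections are current text, so this is a contradiction and not a detail deferred to another document. A separate analysis plan would have to overrule one of the two sections.

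The number of primary outcomes governs what the 5% error and the 80% power refer to. With knowledge alone, both figures have a clear meaning. With two unordered primaries, the error or the power changes according to whether one success is enough or both are needed. Under section 3.20, one of the primary outcomes also has no planning assumption, no operational definition and no named test.

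**Working it through.** **Inputs.** From section 3.6: mean change in knowledge 0.7 (SD 2.21) for intervention and −0.30 (SD 2.33) for control, 80% power, 5% error, 30% attrition. From section 3.7: 1:1 allocation. The sidedness of the 5% is not stated. The correlation between the two scores and the effect on empowerment are not in the protocol, so they are assumptions below.

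**Step 1: reproduce the plan's figure.**

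- Difference: 0.7 − (−0.30) = 1.0.
- Pooled variance: (2.21² + 2.33²)/2 = (4.8841 + 5.4289)/2 = 5.1565, so SD = 2.271.
- n per group = 2 × SD² × (z₀.₉₇₅ + z₀.₈₀)² / difference² = 2 × 5.1565 × (1.960 + 0.842)² / 1.0² = 80.9, rounded up to 81.
- Attrition: 81/(1 − 0.30) = 115.7, rounded up to 116 per group. This matches the protocol.
- A one-sided 5% gives 64 completers and 92 per group, which does not match.

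The stated size therefore uses the whole two-sided 5% for knowledge alone.

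**Step 2: two primaries, either one sufficient, each at two-sided 0.05.** With independent tests, the familywise error is 1 − 0.95² = 0.0975. With correlated tests it is 1 − P(|Z₁| < 1.96 and |Z₂| < 1.96) under a bivariate normal with correlation r:

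| Assumed r | Familywise error |
| --- | --- |
| 0 | 9.75% |
| 0.3 | 9.5% |
| 0.5 | 9.1% |
| 0.7 | 8.3% |
| 0.8 | 7.8% |

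**Step 3: two primaries, both required.** The error stays at or below 5%. With 81 completers per arm, the expected test statistic for knowledge is 1.0/(2.271 × √(2/81)) = 2.80, so its power is Φ(2.80 − 1.96) = 80.0%. If empowerment has the same standardised effect, joint power at r = 0 is 0.80² = 64%. It is 67% at r = 0.3, 69% at r = 0.5 and 73% at r = 0.8.

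**Step 4: two primaries, 5% split equally.** The critical value at two-sided 0.025 is 2.241. Power for knowledge with 81 completers per arm is Φ(2.80 − 2.241) = 71%. Restoring 80% for knowledge takes 2 × 5.1565 × (2.241 + 0.842)² = 98.03, rounded up to 99 completers. That is 99/0.70 = 141.4, so 142 per group and 284 in total. The same sum cannot be done for empowerment, because the protocol gives no inputs for it.

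**The case against.** The strongest reply is that the error inflation is conditional. A reader might infer that the protocol nearly doubles its false-positive rate. The documents do not support that as a statement of fact: no section says that success on either outcome suffices, 9.75% is a ceiling reached only with uncorrelated tests, and there is no inflation if both are required. Handling of multiplicity is also commonly left to a statistical analysis plan, which may exist and is not shown, so its absence is no finding. This part of the reply stands.

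A reader might go further and count two questionnaires at two visits as four chances of success, with an error of about 15% to 17%. That needs four separate tests, an any-one-wins rule and particular correlations. None of these is in the protocol, and the GEE in section 3.12 can model the visits jointly. The figure should not be used. Nor does the text support a claim that anyone intends to pick the primary after seeing results; it only fails to rule this out.

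It is also fair to say that empowerment is a planned outcome: it has an objective, an instrument and scheduled visits. The analysis section does not cover knowledge alone, since the GEE also covers the clinical outcomes. Finally, testing knowledge first at 0.05 and empowerment only after success would keep 5% error and 80% power for knowledge with two outcomes. The protocol states no such order, though, and under it knowledge would be the outcome that decides the trial, which is close to section 3.12.

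None of this removes the contradiction between sections 3.12 and 3.20, or supplies a planning basis and a named test for empowerment as a primary outcome.

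**Conclusion.** The point holds as an internal contradiction that must be resolved. Section 3.12 has one primary outcome and section 3.20 has two, while section 3.6 and the tests named in section 3.12 support only knowledge in that role.

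The size of the problem depends on a success rule that the protocol does not give. An either-one rule puts the familywise error at about 7.8% to 9.8%; a both-required rule leaves joint power at about 64% to 73%. Both ranges rest on assumed correlations of 0 to 0.8, and the second also on an equal standardised effect for empowerment. As written, the stated 5% and 80% hold together only under section 3.12's version. Knowledge is primary in both versions, and the 116 per group is correct for it.

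The visit is a smaller part of the same point. Section 3.12 ties the paired test to 6 months but sets no visit for the between-group t-test. A reader might infer that 6 months is already fixed for the primary comparison; the text does not go that far.

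**What to change.** Make section 3.20 agree with section 3.12: diabetes knowledge as the single primary outcome. State one visit for its between-group comparison. Six months is the natural choice, because the paired test already uses it, but it has to be written in. List empowerment as a secondary outcome in both sections, give it a row in the operational definitions (3.11), and name its analysis in section 3.12. The 232 then stands.

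If the sponsor prefers two primaries, state whether one or both must succeed and how the 5% is handled, name an analysis for empowerment, give planning values for it, and restate the resulting power. For example, a 0.025 split with 81 completers per arm leaves about 71% power for knowledge; restoring 80% for knowledge takes 142 per group.

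The recommended change is wording only, with no added patients, visits or data. Its cost is that empowerment loses its primary label.

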# Methodology

## Study Type and Design

The study design that will be used in this study is a Blocked Randomized Control Trial (RCT) ratio one to one. The samples will be from Klinik Kesihatan Cheras Baru. The study will be conducted and evaluated by the requirement in the Consolidated Standards of Reporting Trials (CONSORT) Statement. (19)

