**Section C for Diabetes empowerment score questionnaire**

Section C will assess general knowledge of diabetes and diabetes self-care. The translated Malay version Diabetes empowerment score test will be used for pre and post-test. For the translated questionnaire, the Cronbach's alpha was acceptable (α=0.760).

A series of web-based education videos will be developed by primary care physicians, dietitian, physiotherapist, occupational therapist, and dentist in English scripts then translated into Malay, Chinese and Tamil.

Expert panellists will edit and review all the web-based educational videos and validate them using a video validation questionnaire with input from endocrinologists, primary care physicians, dietitians, physiotherapists, and occupational therapists and a few patients.

These videos discuss the following topics:

1. Definition and importance of HbA1c.
2. Complications of diabetes.
3. Instructions on self-monitoring blood glucose and the target value.
4. Diabetic medications and side effects.
5. The hypoglycaemia information
6. Diet information pertaining to healthy plates, regular meals, portion sizes, and mindful eating
7. To perform self-foot examination at home.
8. Instruction in home exercise
9. An introduction to eye examinations in diabetes and the need to monitor.
10. The importance of an annual dental check to prevent periodontitis.

Afterwards, the videos will be recorded in Malay, Chinese, Tamil and English with subtitles by the recording by the primary care team. Each video will be about 3 minutes. The technical team will edit the recording.

We will evaluate the feasibility of the videos (clarity of contents and language) with 10 participants. These participants would be type 2 diabetes patients with diverse age groups, ethnicity, and education levels. Their review and feedback will be revised in the videos, if necessary. Once the videos are finalised, they will be uploaded to the social media (e.g TikTok) private account or website for participants to access.

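### The protocol names two different primary outcomes: knowledge alone in section 3.12, knowledge and empowerment in section 3.20, with the sample size built on knowledge only and no named test for empowerment

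*Protocol*

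**What the plan says.** Section 3.12 (Dependent Variables) reads: "In this study, the primary outcome of interest is diabetes knowledge and the secondary outcome is clinical outcome". Section 3.20 (Study Outcome) reads: "The primary outcome of interest are diabetes knowledge and diabetes empowerment", and the same sentence stands in the contents list. In both sections the secondary list holds clinical measures only, so under section 3.12 empowerment has no rank at all.

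The rest of the protocol treats empowerment unevenly:

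- **Present.** Specific objective 4 compares it between and within groups at baseline, 3 and 6 months. Section 3.10 gives it its own questionnaire section (Section C).
- **Absent.** Neither research question in section 1.2 mentions it, and the table of dependent variables in section 3.11 has no row for it.
- **Blurred.** The text on the empowerment form says "Section C will assess general knowledge of diabetes and diabetes self-care", which overlaps with Section B, the knowledge test.
- **Sizing.** Section 3.6 uses one outcome: "mean±sd of knowledge differences for intervention group and control group were 0.7±2.21 and -0.30±2.33".
- **Analysis.** In section 3.12 the independent t test is for knowledge and the paired t test names no outcome. For the model: "Generalized Estimating Equation (GEE) will be used to investigate the effectiveness of diabetes knowledge and clinical outcome, adjusted with covariates". The only threshold is P<0.05.

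**The concern.** Two analysts who follow different sections could report different results from the same data. Suppose knowledge shows no effect and empowerment improves. Section 3.12 gives a negative trial. Section 3.20, read as success on either outcome, gives a positive one. In the reverse pattern section 3.12 gives a positive trial, and section 3.20, read as requiring both, gives a negative one. As written, the choice could be made after the questionnaire scores are known. The 5% error and 80% power in section 3.6 are tied to knowledge and do not carry over unchanged to a pair of primary outcomes.

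**Working it through.** **1. Reproduce the stated sample size.** Inputs from section 3.6: mean change 0.7 (SD 2.21) against -0.30 (SD 2.33), power 80%, error 5%, attrition 30%. Allocation is 1:1 (section 3.1). The sidedness is not stated, so both were tried.

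- Difference = 0.7 - (-0.30) = 1.0.
- Sum of variances = 2.21² + 2.33² = 4.8841 + 5.4289 = 10.313. Pooled SD = √(10.313/2) = 2.271. Standardised effect = 1.0/2.271 = 0.44.
- Two-sided: n = (z for α/2 + z for power)² × 10.313 / 1.0² = (1.960 + 0.842)² × 10.313 = 80.9, so 81 evaluable per group.
- Attrition: 81/(1 - 0.30) = 115.7, so 116 per group and 232 in total. This matches exactly.
- One-sided: 64 evaluable, 92 per group. This does not match.
- Power with 81 per group: 80.0% by the normal formula, 79.6% by the t test.

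So the stated size is right for knowledge as the single primary outcome, tested two-sided at 5%.

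**2. Apply the two-outcome version in section 3.20, each outcome at P<0.05.** The protocol gives no effect or SD for empowerment and no correlation between the scores. Assumptions: the two test statistics are bivariate normal with correlation 0 to 0.9. For power, empowerment has the same standardised effect as knowledge (0.44), hence also 80% power with 81 evaluable.

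- Either suffices: family-wise error = P(at least one of two tests significant when neither outcome has an effect). At correlation 0 this is 1 - 0.95² = 9.75%.
- Both required: joint power = P(both significant). At correlation 0 this is 0.80 × 0.80 = 64%.

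| Correlation | Error if either suffices | Power for at least one | Joint power if both required |
|---|---|---|---|
| 0 | 9.75% | 96% | 64% |
| 0.3 | 9.5% | 93% | 67% |
| 0.5 | 9.1% | 91% | 69% |
| 0.7 | 8.35% | 89% | 71% |
| 0.9 | 7.0% | 85% | 75% |

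Each rule breaks one property and not the other. With either sufficing, the error exceeds 5% but the chance of a success is not reduced. With both required, the error stays at or below 5% and power drops.

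**3. Sensitivity to the assumed empowerment effect.** If empowerment had only 60% power, joint power at correlation 0 would be 0.80 × 0.60 = 48%. The error figures do not depend on this assumption; the joint power figures do.

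**4. What two primary outcomes would need, under the same equal-effect assumption.**

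- Splitting alpha at 0.025 each lowers power for knowledge with 81 evaluable to 71.3% (70.5% by the t test). Restoring 80% needs (2.241 + 0.842)² × 10.313, so 99 evaluable; 99/0.7 gives 142 per group, 284 in total.
- Requiring both, with 80% joint power at correlation 0, needs √0.80 = 89.4% power for each: 107 evaluable; 107/0.7 gives 153 per group, 306 in total.

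**The case against.** The best defence is that section 3.6 ties its 80% and 5% to knowledge, and for that claim the arithmetic is exact. The analysis plan may exist as a separate document, and a success rule and multiplicity method commonly sit there. Both points stand: the sample size is not wrong, and the lack of a multiplicity rule is not counted here as a fault of its own. Neither point removes the contradiction. A separate plan could add a rule, but the protocol would still name two different primary outcomes.

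A reader might infer more than the document supports:

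- *That every named test covers knowledge only.* The GEE also covers the clinical outcomes, and the paired t test names no outcome. What holds is that no named test mentions empowerment.
- *That the 5% error and the 80% power fail together.* No single success rule does both.
- *That the rest of the protocol fits only one primary outcome.* Specific objective 4 and Section C of the questionnaire give empowerment a real place, so intent cannot be read off with certainty.
- *That the error nearly doubles in any case.* That is the low-correlation end. If the two scores are strongly related, as the Section C wording could suggest, it is nearer 7%.
- *That the trial is open, which makes a late choice more likely.* The protocol does not state its blinding status, so the point does not rest on this.

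**Conclusion.** The contradiction is real and concerns what the trial will conclude, so it should be resolved before analysis. Sections 3.12 and 3.20 name different primary outcomes, and under section 3.12 empowerment has no rank although it is measured and compared. The sizing supports the single-outcome version only. Following section 3.20 at P<0.05 each means either a family-wise error of about 9.8% to 7.0% (correlation 0 to 0.9) or joint power below 80%. Which of the two applies depends on a rule the protocol does not state. The error range needs only the assumed correlation. The joint power range of 64% to 75% also needs an assumed empowerment effect equal to that for knowledge, so it illustrates the loss and is not a figure to write into section 3.6.

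**What to change.** Make section 3.20 and the contents list agree with sections 3.12 and 3.6:

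- Name knowledge as the single primary outcome, tested at two-sided 0.05, and say that the 80% power refers to it.
- List empowerment as a secondary outcome in sections 3.12 and 3.20, give it a row in the section 3.11 table, and add it to the outcomes analysed by GEE.
- Correct the Section C description so that it says the form measures empowerment.
- State that an empowerment result cannot replace a negative knowledge result.

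This costs wording only. The 116 per group stands, and no data or patients are added. The one loss is that empowerment cannot carry the main claim.

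Which section reflects the intent is for the sponsor to say. If two primary outcomes are meant, the protocol must state whether either or both must succeed, give an effect and SD for empowerment with their source, and restate the power in section 3.6 from those figures. That option either accepts lower power or needs more patients; the totals of 284 and 306 above show the order of size under the equal-effect assumption only.
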